##### Cohort Client Follow-Up (Nested Study)

A random selection of eligible client participants (100 from each group) will form a cohort sub-sample who will be contacted via telephone and invited to complete the cohort follow-up survey. Eligible clients will be those who completed the baseline survey and, at that time, consented to be contacted regarding the cohort follow-up; and either (1) were offered the healthy choices consultation (if in the intervention group) or (2) had at least one mental health consultation in the preceding 9 months (if in the control group).

#### 2.3.3. Mental Health Clinicians

It is intended that all clinicians (psychiatrists, psychologists, social workers, peer workers, nurses, and other disciplines) working in the services allocated to the intervention group received the intervention. Clinicians of intervention and control services who provide direct clinical care to clients and are over 18 will be eligible to take part in online surveys on two occasions: baseline and follow-up (cross-sectional surveys, independent samples). At each data collection point, clinicians will be sent an email from their service manager providing the information statement and containing a link to the survey if wish to complete it (approximately 20 clinicians per service on average). The initial survey questions will confirm clinician eligibility.

### 2.4. Intervention

A multi-component clinical practice change intervention will be implemented in the intervention group services for 9 months. This timeframe was chosen based on consultation with participating LHDs for logistical reasons (i.e., enabling delivery of the multi-component intervention). The intervention will involve two parts: (a) a model of providing preventive care; and (b) implementation strategies to support model implementation. Figure 2 displays these two parts, and they are described in further detail in Section 2.4.2.

The key elements of the model of care and implementation strategies were pre-determined by the research team based on relevant evidence [15,16,17,31,32,33,34]. These key elements are also displayed in Figure 2. These elements will provide a foundation for the co-development process (described below), which will explore how these may be implemented.

#### 2.4.1. Co-Development Process

At project commencement, a working group for each LHD will be established, with representation from the research team, service managers and clinicians. These working groups will aid in tailoring the intervention delivery to each service’s usual procedures and to local availability of behaviour change support options. A series of initial meetings will be conducted to provide input into intervention design. This will include reviewing the described model of care pre-determined by the research team (to ensure integration with usual service delivery), with a particular focus on the implementation support, to consider how the implementation strategies will be designed and delivered.

Table 1 provides an overview of the pre-determined elements of the intervention that will provide a foundation for co-development and examples of elements that will be determined through co-development. The tailoring of the model of care and implementation strategies will occur predominantly at the LHD level (e.g., how/where information about client risk factors will be embedded into the existing care management plan); however, some tailoring may be necessary at the service level due to unique service characteristics (e.g., delivery of clinician training within existing training opportunities that are unique to each service). The model of care and implementation support are flexible in terms of delivery to allow for changes that could be needed due to COVID-19 restrictions on service delivery or general restrictions. The working groups will continue to provide advice and guidance throughout the 9-month intervention period.

During the development and implementation phases, input will be sought from Aboriginal representatives to ensure intervention development and implementation is culturally appropriate, as well as mental health consumer and peer-worker representatives to appropriately consider consumer experiences and perspectives. This will firstly be undertaken through separate meetings with these representatives (identified by the participating LHDs) or with the existing consultative groups that exist in some of the participating LHDs. Following this, the research team will ask representatives their preferred way to continue to contribute to intervention development and implementation. This could include membership on the working group, through seeking advice separately, e.g., during existing meetings of consultative groups within the LHDs. Feedback will also be sought on the client activation materials (described in Table 1).

#### 2.4.2. Model of Preventive Care

The model of care consists of three key components, which will be delivered to clients of mental health services during the 9-month intervention period (see Figure 2 for summary):‘Healthy choices’ consultation

A 40 minute consultation dedicated to addressing chronic disease risk factors and provided by a ‘Healthy Choices Clinician’ (HCC) will be offered to adult clients. The consultation will be framed around the evidence-based AAR framework [15,16,17] for key chronic disease risk factors (smoking, nutrition, alcohol, physical activity, and overweight/obesity) and collaboratively setting behaviour change goals with the client. The consultation will incorporate evidence-based behaviour change techniques, such as motivational interviewing [41]. The HCC could have a range of professional backgrounds (e.g., occupational therapist, dietician, nurse, and social worker) and will have expertise in health behaviour change strategies. The fractional HCC appointment (hours per week) required in each service will be determined through co-development (proportional to number of clients and staff). HCCs will complete training in intervention delivery according to a manualised protocol. The consultation, tailored to each client, will include:Assessment: Clients will be asked about their current engagement in risk factors, with risk status determined in accordance with the Australian National Health and Medical Research Council Guidelines (Table 2) [42,43,44,45,46].Brief advice and goal setting: Information will be provided regarding how the client’s risk factors compare to Australian guidelines. Tailored motivational interviewing strategies will be used to foster client desire to change their risks and build agency. Clients will be encouraged to identify at least one health improvement goal in line with their risk status and/or desired areas for improvement.Referral: Clients will be offered referrals to services that provide behaviour change support, based on their risk status [42,43,44,45,46] and/or their identified health improvement goals. This could include referral to services, such as state-level telephone services (e.g., the NSW Quitline [47] and NSW Get Healthy Information and Coaching service [48]) and local providers (e.g., GP, dietician, support groups, and walking groups).

ii.Chronic disease risk information embedded in the care plan

Mental health care management plans are an existing part of mental health service delivery for all participating LHDs. Additional content will be embedded into this existing care plan in the client’s electronic record, including the client’s risk factors, goal(s) for change, and any referrals to behaviour change supports (offered and accepted). The plan will serve as a basis for the client’s clinician to provide continued preventive care (described below).

iii.Continuation of preventive care by mental health clinicians

Clinicians will provide ongoing follow-up and support for chronic disease risk factors in their routine consultations. After a client has had a ‘healthy choices’ consultation, the HCC will liaise with the client’s treating mental health clinician regarding the appointment content and outcomes, and the clinician will review the relevant content of the care plan. Commencing at the following scheduled appointment with the client, the clinician will provide ongoing follow-up and support. This will include behaviour change support, such as encouraging and motivating desire for behaviour change, building agency for change and monitoring progress towards goals. Clinicians will encourage connection with referral services, by monitoring uptake of referrals provided and initiating further support as required. Clinicians will regularly review and update the care plan as required. The service will define how clinician review of their clients’ risk behaviour goals and progress will occur on a regular basis.

#### 2.4.3. Implementation Support Strategies

Supported by findings of Cochrane reviews, evidence-based implementation strategies [31,32,33,34] will be provided over a 9-month period to support the intervention services in implementing the model of care as part of routine practice.

Based on the Cochrane review evidence, ongoing stakeholder consultation, and the team’s previous trials [28,49], the following strategies will be implemented (described in detail in Table 1):Clinical support personnel: The HCC embedded within each service to support care delivery and provide education to staff. Implementation support officers (members of the research team; one allocated to each LHD) will support HCCs in this role.Leadership and consensus processes: Leaders in each LHD (e.g., service managers) will communicate their strong support for the project. Within each LHD, an advisory group will be established to oversee project direction and implementation.Enabling systems: Content from the healthy choices consultation will be integrated into the existing mental health care plan, which will be reviewed regularly in clinical review meetings.Clinician education and training: Training sessions and resources will be provided to cases managers regarding strategies for supporting client behaviour change, the importance of addressing chronic disease risks and the logistics of model implementation. Training of the HCC in their role.Audit and feedback: An update of progress will be prepared by the HCC and discussed in advisory and working groups to review progress and consider recommended actions.Client activation strategies: Resources to build behaviour change agency and self-management skills, and to inform clients about the new model of care (e.g., posters in waiting rooms, client diaries, and educational brochures).

### 2.5. Control

Services randomised to the control condition will continue to provide preventive care for chronic disease risk factors in accordance with their usual practices.

### 2.6. Measures

Study measures are described in detail below. In summary, the primary outcomes are client-reported receipt of preventive care (AAR framework) for multiple chronic disease risks. The secondary outcomes are client receipt of individual AAR elements for each chronic disease risk behaviour and weight; conversations with mental health clinician about behaviour change goals; and client health behaviour change measures (risk factor variables and attempts, confidence and readiness to change behaviours). Supplementary-Table S2 contains the SPIRIT schedule: the recommended schematic diagram of the study measures and time periods.

#### 2.6.1. Primary Trial Outcomes

The primary outcomes are the proportion of clients who reported receiving elements of the AAR framework of preventive care: (1) assessment for all chronic disease risk behaviours (tobacco smoking, inadequate fruit and vegetable consumption, harmful alcohol use and physical inactivity), (2) brief advice for all relevant risk behaviours (Table 1), and (3) referral to at least one behaviour change service for a relevant risk behaviour.

#### 2.6.2. Secondary Trial Outcomes

##### Client Receipt of Preventive Care

The secondary outcomes regarding preventive care are client-reported receipt of the individual elements of preventive care for the individual AAR elements for each chronic disease risk behaviour and weight, and conversations with their mental health clinician about their behaviour change goals. Clients will be asked to report their receipt of each preventive care element (assessment, advice and referral) for each individual risk factor (tobacco smoking, inadequate fruit and vegetable consumption, harmful alcohol consumption, physical inactivity, and overweight/obesity) from their mental health service in the previous 9 months (total of 15 items). Participants will also be asked whether their mental health clinician spoke to them in the preceding 9 months about their goals for behaviour change (yes/no/do not know).

##### Client Behaviour Change

Clients will self-report their levels of chronic disease risk factors over the previous month, specifically:Whether they smoked any tobacco products (yes, daily; yes, at least once a week; yes, less than once a week; not at all, quit less than 6 months ago; not at all, quit 6 months or more ago; not at all, never smoked; do not know) and how many cigarettes they smoked per day;How many serves of fruit (open ended) and vegetables (open ended) they typically consumed per day;How often they consumed alcohol in the last month (never, I do not drink, e.g., never have; none in the last month, e.g., nil last month, drinks occasionally; once a month; 2-to-4 times a month; 2-to-3 times a week; 4 or more times a week; do not know). Those who report consuming alcohol in the previous month will be asked to report how many standard drinks they consumed on a typical drinking day (open ended) and how often they consumed five or more standard drinks on one occasion (never; less than monthly; monthly; weekly; almost daily; daily; do not know) (items adapted from the Alcohol Use Disorders Identification Test (AUDIT-C) for Alcohol Use [50]);How many minutes they engaged in walking, moderate physical activity, vigorous physical activity, and strength activities in a typical week (items adapted from the International Physical Activity Questionnaire [51]);Their current weight (kg) and height (cm).

Participants will also be asked whether they made any attempts to change each of the chronic disease risk factors in the previous 9 months (yes/no/do not know). For each risk factor, participants will be asked to report their readiness to change by selecting which option best describes them: I never think of changing (risk factor); I sometimes think about changing (risk factor); I have decided to change (risk factor); I am already trying to change (risk factor); my (risk factor) has changed [52]. Participants will report on a 1 to 10 scale how confident they are in their ability to make changes relevant to each risk factor [53,54]. For these measures, smoking items will be asked of participants who reported currently smoking and alcohol items of participants who report consuming any alcohol.

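### The smoking attempt and readiness items go only to current smokers, so cohort clients who quit by follow-up drop out and the described between-group difference is attenuated

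*Protocol article*

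**What the plan says.** Section 2.6 of the Protocol article lists among the secondary outcomes "client health behaviour change measures (risk factor variables and attempts, confidence and readiness to change behaviours". Section 2.1 assigns client behaviour change outcomes to the nested cohort follow-up.

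Section 2.6.2 (Client Behaviour Change) sets out the items:

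- **Behaviour levels:** "Clients will self-report their levels of chronic disease risk factors over the previous month". The smoking answers keep people who have stopped apart from never smokers: "not at all, quit less than 6 months ago; not at all, quit 6 months or more ago; not at all, never smoked".
- **Attempts:** participants are asked "whether they made any attempts to change each of the chronic disease risk factors in the previous 9 months".
- **Readiness:** the last two of the five options are "I am already trying to change (risk factor); my (risk factor) has changed".
- **Filter on attempts, readiness and confidence:** "smoking items will be asked of participants who reported currently smoking and alcohol items of participants who report consuming any alcohol".

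No such filter is stated for fruit and vegetables, physical activity or weight.

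On timing, Section 2.4 says: "A multi-component clinical practice change intervention will be implemented in the intervention group services for 9 months". The attempt item therefore looks back over a period as long as the intervention.

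Section 2.8 models smoking status (yes/no) and drinks per week, among other measures, in the cohort. It does not list attempts, readiness or confidence, so these fall under its provision that remaining measures are reported descriptively.

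**The concern.** The attempt item covers 9 months, but whether a client is asked it depends on smoking status at the interview. A client who smoked at baseline, tried to stop during the intervention and succeeded is a clear case of an attempt, yet is routed past the item. The same client cannot choose the readiness option for having changed, although a smoker who has merely cut down can.

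Current smoking at follow-up is a post-randomisation state that the intervention aims to change, since it offers cessation advice and referral. Restricting the item to current smokers removes successful attempters from both numerator and denominator, and removes more of them where more people quit. At stake is whether the reported percentages for two named secondary measures compare like with like.

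**Working it through.** **The plan's own figure.** Section 2.7 expects 60% of 200 selected clients to complete the cohort follow-up: 200 × 0.60 = 120, or 60 per group. This reproduces. The point does not depend on any power calculation.

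**Inputs.** The protocol gives no smoking prevalence, attempt rate or quit rate. All rates below are assumptions for illustration.

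**Formula.** Among clients who smoked at baseline, let *a* be the true proportion who attempted to quit and *q* the proportion who have quit by follow-up. Assume that everyone who quit made an attempt. Among those still smoking, the proportion reporting an attempt is (a − q)/(1 − q).

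**Results** (intervention v control):

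| True attempts | Quit | Seen, intervention | Seen, control | True difference | Seen difference |
|---|---|---|---|---|---|
| 50% v 40% | 12% v 6% | 0.38/0.88 = 43.2% | 0.34/0.94 = 36.2% | +10 | +7.0 |
| 50% v 40% | 15% v 5% | 0.35/0.85 = 41.2% | 0.35/0.95 = 36.8% | +10 | +4.3 |
| 50% v 40% | 20% v 5% | 0.30/0.80 = 37.5% | 36.8% | +10 | +0.7 |
| 45% v 40% | 10% v 5% | 0.35/0.90 = 38.9% | 36.8% | +5 | +2.0 |
| 60% v 40% | 15% v 5% | 0.45/0.85 = 52.9% | 36.8% | +20 | +16.1 |
| 45% v 40% | 15% v 5% | 0.30/0.85 = 35.3% | 36.8% | +5 | −1.5 |

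**When the sign reverses.** With subscripts I and C for intervention and control, the seen difference is negative when q_I − q_C > (a_I − a_C)(1 − q_C)/(1 − a_C). With 40% attempts and 5% quitting in control, the multiplier is 0.95/0.60 = 1.58, so quitting must differ by more than 1.58 times the difference in attempts. For a 5-point attempt difference that is 7.9 points; for a 10-point difference it is 15.8 points. The last row (a quit difference of 10 points) crosses this line and the others do not. That row implies success per attempt of 15/45 = 33% v 5/40 = 12.5%.

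**When there is no attenuation.** If quitting is equal, the seen difference is slightly inflated: with 5% in both arms, 0.45/0.95 − 0.35/0.95 = 0.10/0.95 = 10.5 points. Attenuation therefore comes from excess quitting in the intervention arm. For 50% v 40% attempts and 6% quitting in control, the break-even solves 0.60/0.94 − 0.50/(1 − q_I) = 0.10, giving q_I = 7.1%.

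**Numbers of people.** If 30% to 60% of the 60 completers per group smoked at baseline, that is 18 to 36 smokers. Quitting of 6% to 12% is then 0.06 × 18 = 1.1 to 0.12 × 36 = 4.3 people per group.

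**The case against.** The strongest reply is that little rests on these items. Attempts, readiness and confidence are not among the modelled cohort measures, so no planned between-group test uses them. Successful quitting is not lost from the trial: every client is asked smoking status, and smoking status is modelled in the cohort. Because the cohort is longitudinal, a baseline smoker who later reports having quit is identifiable, and an analysis rule could count that client as an attempter without asking the item. The primary outcomes and the economic analysis, which uses them, are unaffected. All of this stands and limits the weight of the point. It does not make the described percentages right: as written, they compare groups selected by their own result.

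A reader might infer three stronger things that the document does not support.

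- **That the difference would change sign.** This needs quitting to differ well beyond attempts. The protocol gives no rates that would make it likely, and the one assumed case that reverses requires a large gap in success per attempt.
- **That alcohol is affected in the same way.** The filter there is any consumption, with no time window, and Table 2 defines the risk as harmful use. Clients who cut down are still asked about attempts and can report having changed. Only those who stop altogether are lost. How the answer for occasional drinkers with none in the last month is routed is not stated.
- **That follow-up routing certainly uses same-survey status.** This is the natural reading but is not said outright. If baseline status were used in the cohort follow-up, the problem would not arise there, and one sentence would settle it.

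**Conclusion.** The point holds in a limited form. On the natural reading of the filter, cohort clients who smoked at baseline and quit by follow-up are left out of the smoking attempt and readiness measures. If the intervention increases quitting beyond a small margin, the described difference in attempts is attenuated: +10 points becomes about +7 with 50% v 40% attempting and 12% v 6% quitting. Readiness is distorted in the same direction, because those excluded are people who would choose its top category. For alcohol this applies only to clients who stop drinking altogether.

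The size rests on assumed rates and on every quitter having made an attempt; the mechanism does not depend on the particular rates. The matter should be settled before follow-up interviewing, because answers that were never asked for cannot be recovered later.

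**What to change.** - **Cohort follow-up:** route the smoking and alcohol attempt and readiness items on baseline use plus any current use. Count a baseline smoker who reports having quit since baseline as having made an attempt and as having changed.
- **Alcohol filter:** state whether a client who drinks occasionally but had none in the last month counts as consuming any alcohol.
- **Cross-sectional follow-up, if these items are compared there too:** ask anyone who smoked or drank within the previous 9 months, and count only stops within that window. The existing smoking answers split at 6 months, so the longer-ago category mixes quits inside and outside the 9 months. A direct question on use in that period is needed.
- **Confidence:** this may stay restricted to current users, provided the reports label it so.

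The cost is a change of skip logic in the telephone interview and a few extra items for clients who have recently stopped. Sample size, design and the modelled outcomes do not change.

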#### 2.6.3. Client Sociodemographic Characteristics

Client age, gender, postcode, and number of community mental health appointments within the previous 9 months will be obtained from the service electronic records. In the surveys, participants will report their primary psychiatric diagnosis, highest educational level, employment status and relationship status.

